### Enrollment and follow-up

GPs will be first enrolled, trained, and invited to complete the same KAP questionnaire on antithrombotic treatment three times before and after the training and at the end of the study. In the last month, one GP in each community health center of the intervention group will be randomly selected for a semi-structured interview. After training, GPs can enroll patients with AF that meet all the inclusion criteria and none of the exclusion criteria into this study, after signing the informed content. The follow-up will last for 12 months. Within the first week and the fourth, eighth, and twelfth months after enrolling, patients will be required to finish the PSQ-18 questionnaires. Patients will be contacted by telephone at the last week of a month or the first week of the next month, if they do not revisit their doctors in that month. One free INR point-of-care testing (POCT) collecting finger-stick blood will be provided to patients who complete all the 1 year time’s follow-up and the reasons for patients not finishing the study will be collected if possible. The study flowchart is shown in Fig. 4.

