**Methods:**

This study will be a prospective cluster randomized controlled trial, conducted among 14 community health centers in Shanghai which were randomized as the intervention group and control group in a ratio of 1:1. The intervention group will use the CDSS in the consultation of patients with AF and the control group will maintain their usual care. The trial will include 498 patients with AF and the follow-up period will be 12 months. The primary outcome is set as the proportion of antithrombotic treatment prescriptions in agreement with recommendations in the latest China’s AF-related guidelines. The secondary outcomes are the frequency of consultation, the compliance rate of international normalized ratio (INR) in patients with warfarin, stroke morbidity, treatment compliance, medication satisfaction, and the cost-benefit analysis. Per-protocol (PP) analysis and the intention-to-treat (ITT) analysis will be conducted.

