## Methods

### Study design

This study is a prospective, paralleled, open-label, single-center cluster randomized controlled trial. The Ethics Committee of Zhongshan Hospital approved the present study protocol (Approval Number: B2021-579(2)). The study was registered in the Chinese Clinical Trial Registry, International clinical trials registry platform of the World Health Organization (Registration Number: ChiCTR2100052307). This protocol was designed and described according to the standard protocol item- Recommendations for Interventional Trials–Artificial Intelligence (SPIRIT-AI) extension published in 2019 [26] (Additional file 1) and the consolidated standards of reporting trials (CONSORT) 2010 statement: extension to cluster randomized trials [27].

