#### Allocation concealment mechanism

The allocation results of each community health center were told to the administrators by telephone. Each administrator only knows the result of his or her own site.

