#### Blinding

The researchers, participants, and data analysts will not be blinded, but the participants will not be allowed to know the outcomes of this study.

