#### Preparation

Prior to be used, the CDSS will be embedded into the HIS of community health centers in the intervention group. The GPs will be trained in the use of the CDSS within the intervention group by developers from Ping An Healthcare and Technology Co.Ltd., and GPs of both groups will be trained in AF management by the researchers. After training, the training materials will be bound into a handbook and provided to the GPs for free.

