#### Usage

After training, GPs in the intervention group can use the CDSS to manage patients with AF. It will capture the diagnosis code automatically after being linked with HIS, so when a patient is diagnosed as AF or atrial flutter, a pop-up reminder will show up. The interface of the CDSS will be presented after GPs click on the pop-up window. Referral indicators will be showed first to remind GPs of judging whether the patient needs to be referred to a superior hospital. The referral indications included immediate and general indicators [28]. The detail introductions are separated into initial and follow-up visit patients.

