## Trial status

This publication is based on version 1.2 of the trial protocol dated Oct. 15, 2021. It is planned to enroll participants in Jan. 2022, and to follow up until Jan. 2023 (Fig. 5).

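### Unblinded GPs choose and consent patients after allocation, and only one arm has an AF-code prompt, so the enrolled patients can differ by arm

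*Protocol article*

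**What the plan says.** All references are to the Protocol article.

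- **Allocation came first and was disclosed.** The Abstract (Methods) describes a trial "conducted among 14 community health centers in Shanghai which were randomized as the intervention group and control group in a ratio of 1:1". Under Allocation concealment mechanism: "The allocation results of each community health center were told to the administrators by telephone". Both are in the past tense, while patient enrolment lay ahead (Trial status): "It is planned to enroll participants in Jan. 2022, and to follow up until Jan. 2023".
- **Training reveals the arm.** Under Preparation: "The GPs will be trained in the use of the CDSS within the intervention group by developers". GPs in both groups receive the AF-management training.
- **No blinding.** Under Blinding: "The researchers, participants, and data analysts will not be blinded". Settings and participants counts GPs among the participants.
- **The same GPs then recruit.** Under Enrollment and follow-up: "After training, GPs can enroll patients with AF that meet all the inclusion criteria and none of the exclusion criteria into this study".
- **Only one arm is prompted.** Preparation places the CDSS in the hospital information system (HIS) of intervention centres. Under Usage: "when a patient is diagnosed as AF or atrial flutter, a pop-up reminder will show up". Control centres keep usual care, and no matching prompt is described for them.
- **Primary outcome.** Outcomes defines it as agreement between the doctor's anticoagulation decision for newly diagnosed patients and the system's recommendation. Referral of indicated patients, and withholding where there is no indication or a contraindication, also count as agreement.

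**The concern.** Cluster randomisation balances centres in expectation. It does not balance patients who are picked and consented afterwards by someone who knows the arm. Here the GP who recruits is also the GP whose prescribing is the endpoint, and that GP knows whether the CDSS is available.

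Two routes can make the enrolled groups differ:

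- **Choice and consent.** A GP who knows the arm may invite different patients, or present the study differently, and patients may accept at different rates.
- **Prompting.** Intervention GPs are reminded at the moment a code is recorded and control GPs are not. The Background describes usual care as a setting in which many GPs steer clear of AF. Under Expectation of results, the authors expect the tool to raise the share of patients who accept AF management in primary care. A tool that changes who accepts management can also change who is enrolled.

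Part of the difference in the primary outcome could then reflect who was enrolled rather than what the CDSS did.

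**Working it through.** **1. The plan's own sample size.** Inputs from Sample size: control 12.64%, intervention 28%, ICC 0.02, power 90%, two-sided alpha 0.05, seven centres per arm, 30 patients per control centre, 10% loss.

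- Planned effect: 28 − 12.64 = 15.36 points.
- Pooled two-proportion formula: 143 per arm. Design effect 1 + (30 − 1) × 0.02 = 1.58. 143 × 1.58 = 225.9, so 226 per arm and 452 in total, close to the stated 448.
- Exact match: control 7 × 30 = 210, leaving 448 − 210 = 238, or 34 per intervention centre (inferred, not stated). With unpooled variance, 0.1264 × 0.8736 × 1.58 / 210 + 0.28 × 0.72 × 1.66 / 238 = 0.00224, so the standard error is 0.0473. Then 0.1536 / 0.0473 − 1.96 = 1.29, which is power 90.1%.
- Loss: 448 / 0.90 = 497.8, so 498.

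The stated sizes reproduce. The point concerns bias and leaves them unchanged.

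**2. Order of events.** Randomise centres → tell administrators → train GPs (CDSS training in one arm) → unblinded GPs select, consent and enrol. Every step is stated. The concealment text covers who learns a centre's result, not patient recruitment.

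**3. Illustration of size.** Let a share x of intervention enrolees be replaced by patients certain to be concordant, with no selection in the control arm. If the displaced patients had concordance rate r, the intervention rate rises by x(1 − r). The shares x are assumed; no passage supplies them. For r, take 28% (the planned intervention rate holds) or 12.64% (the CDSS has no effect).

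| x | r = 28% | share of 15.36 | r = 12.64% | share of 15.36 |
|---|---|---|---|---|
| 5% | 0.05 × 0.72 = 3.6 points | 23% | 0.05 × 0.8736 = 4.4 points | 28% |
| 10% | 0.10 × 0.72 = 7.2 points | 47% | 0.10 × 0.8736 = 8.7 points | 57% |

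With 238 intervention patients, 5% is about 12 people and 10% about 24.

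**4. Illustration for the test.** Assume no true effect, a control rate of 12.64%, 224 per arm, and design effect 1 + 31 × 0.02 = 1.62. The effective size is 224 / 1.62 = 138 per arm. If case mix alone raised the intervention rate by 2, 5 or 8 points, the chance of a significant result favouring the CDSS would be about 7%, 21% or 43%, against a nominal 2.5%. These shifts are also assumed.

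**The case against.** Several stronger readings are tempting, and the documents do not support them.

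- **That the pop-up finds AF.** It reacts to a code already entered. It reminds the GP about a coded patient and detects no undiagnosed case.
- **That it flags every coded patient.** Statistical analysis plans a subgroup analysis by whether the CDSS is in all general clinics or only in the AF special consulting room. In the latter setting, patients seen elsewhere may trigger nothing.
- **That the bias must favour the CDSS.** Enrolling willing patients in the intervention arm would inflate the effect, but selection in the control arm could shrink it. Because referral and justified withholding count as agreement, being easy to anticoagulate is not the same as being concordant. A story in which control GPs enrol already treated patients also fits poorly with an outcome defined on new diagnoses.
- **That missing covariates or sampling detail is itself an error.** A covariate list, consecutive sampling or a screening log may stand in the full protocol or analysis plan, which are not shown.

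Shared eligibility criteria, the one-year registration rule and AF training in both arms also limit the risk.

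These objections narrow the mechanism and remove any claim about direction. They leave the stated sequence intact: recruitment by unblinded GPs after allocation, with a prompt in one arm only. A consecutive-sampling rule in an unseen document would reduce the exposure, but recruitment would still follow allocation and be done by GPs who know the arm.

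**Conclusion.** The concern holds as a risk of post-allocation selection built into the stated order of events. The mix of enrolled patients can differ by arm, and the primary comparison is exposed to that difference. Direction and size are unknown.

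The figures of 3.6–4.4 points and 7.2–8.7 points show only that a small displacement would matter against a 15.36-point target. They rest on assumed shares of 5% and 10%, on replacements who are all concordant, on no selection in the control arm, and on every enrolee counting in the primary outcome. They do not estimate the bias in this trial. The change should be made; it does not affect the sample size.

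**What to change.** 1. In all 14 centres, identify candidates with the same HIS query on the ICD-10 codes in Additional file 3, independent of the pop-up. Repeat it during recruitment, for example weekly. A single query would return mainly established cases, whereas the primary outcome concerns new diagnoses.
2. Invite listed patients consecutively until the centre's quota is met.
3. Record and report the numbers eligible, invited, refused and enrolled by arm.
4. Adjust the primary, cluster-adjusted model for age, sex, and stroke-risk and bleeding-risk scores, using data dated before the enrolment consultation. Do not adjust for anticoagulants prescribed at the enrolment visit: for a newly diagnosed patient, that prescription can be the outcome itself.

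If enrolment has already begun, the same query can still be used to compare enrolled with eligible patients in each arm.

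Cost: a recurring query and a log per centre, which is modest administrative work, plus wording for the model. Adjustment reduces only measured imbalance and cannot correct for unmeasured willingness, so the common candidate list and consecutive invitation matter most.

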##### Follow-up visit patients

The follow-up patient management interface is shown in Fig. 3a and the example of result assessment is seen in Fig. 3b. For those with a recent stroke or bleeding, the CDSS will advise referring the patients and for those without, patients treated with NOAC or with no anticoagulants will be selected for continual follow-up and patients treated with warfarin will be provided recommendations based on their recent INR values.

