### Outcomes

The primary outcome is the proportion of antithrombotic treatment prescriptions, in agreement with recommendations in the AF guidelines. It is defined as the agreement rate between the doctor’s anticoagulation prescriptions for newly diagnosed patients and the system’s recommendations, including prescribing anticoagulation drugs or recommending referral to superior hospitals for patients with anticoagulation indications, and refraining from anticoagulation for patients without such indications or with contraindications.

The safety outcomes, such as the incidence of bleeding events, all-cause mortality and in-patient events related to AF or AF complications will be reported. Referring to the Guideline of stroke prevention in Chinese patients with atrial fibrillation (2017), bleeding events are classified as minor and major bleeding [4].

The secondary outcomes contain seven items:

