### Data collection and management

Patients’ basic information will be collected by GPs with a questionnaire. Patients’ information during follow-up will be accessible in the health records and supplements by questionnaires if necessary. The data from the questionnaires will be generated in each follow-up, the follow-up date will be indicated, and the questionnaires will be signed by the investigators and double-entered into the Epidata3.0 database by two researchers. The interview content from GPs will be recorded by audio and verbally at the same time after getting informed consent. Two researchers will sum up the conversation and extract the key information related to the study aim independently. Disagreements will be resolved through discussion or by a third person. This study has no composition of data monitoring committee (DMC) because other data will be reserved in the information security department as parts of patients’ medical records. After completing the follow-up, we will apply to the Network Information Security Center of Baoshan District and Jing’an District Health Commission. The codes of the CDSS will not be accessible at any time except installation and necessary maintenance. When installing the CDSS, developers will cooperate with the programmers of HIS providers and minimize the risk of data leakage. If there are any bugs or data leakage, all people will stop using the CDSS until the problem is solved and the ethics committee approves resumption. The GPs can contact the developers and researchers at any time if they encounter any difficulties and a response will be given within 24 h. For severe adverse events, researchers will report them to the ethics committee within 24 h. If it is attributed to the CDSS, the ethics committee, and the principal investigator (PI) can terminate prematurely and conduct interim analyses. And we will compensate those who suffer harm in accordance with the Chinese law, if necessary.

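### Detection of minor bleeding and TIA can differ by arm: a visit cancels the telephone contact common to both arms, and only intervention GPs have a follow-up pathway that turns on recent stroke or bleeding

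*Protocol article*

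**What the plan says.** All references are to the protocol article.

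- **Where the tool is.** Under Preparation, "the CDSS will be embedded into the HIS of community health centers in the intervention group". The abstract's Methods paragraph says that "the control group will maintain their usual care".
- **What the tool does at follow-up.** Under Follow-up visit patients: "For those with a recent stroke or bleeding, the CDSS will advise referring the patients". Patients without such an event go on to continued follow-up or INR-based advice. No corresponding step is described for control visits.
- **The contact common to both arms.** Under Enrollment and follow-up, the monthly call is made only "if they do not revisit their doctors in that month". The text does not say who calls or what is asked.
- **Source of follow-up data.** Under Data collection and management: "Patients’ information during follow-up will be accessible in the health records and supplements by questionnaires if necessary". The same section adds: "The data from the questionnaires will be generated in each follow-up". It also foresees an application to the two districts' network information security centre after follow-up.
- **Named patient questionnaire.** The only one scheduled is the PSQ-18, a satisfaction instrument, in the first week and at months 4, 8 and 12.
- **Outcomes.** "The safety outcomes, such as the incidence of bleeding events, all-cause mortality and in-patient events related to AF or AF complications will be reported". Bleeding is classified as minor or major. Stroke, including TIA, is a secondary outcome, and so is frequency of consultation.
- **Blinding.** Researchers, participants and analysts are all unblinded.

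**The concern.** A minor bleed or a TIA often enters a record only because someone asked. The one patient contact described as identical in both arms is withdrawn in the months when the patient is seen, and those are the months in which the two arms work differently. The intervention GP uses a pathway that cannot take its branch unless recent stroke or bleeding status is known. The control GP follows usual care. Whether a supplementary questionnaire is needed is then judged by people who know the allocation.

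The mix of visits and calls may also shift. Consultation frequency is an outcome, and the section on expected results predicts more patients accepting AF management in primary care under the CDSS. If so, intervention patients would move from the common telephone route to the route that differs by arm.

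At stake is the reading of the bleeding and stroke/TIA results. Better capture in the intervention arm would make a neutral tool look as if it caused bleeding, and would hide part of any stroke benefit. The planned Kaplan-Meier and Cox analyses and the adjustment for clustering do not correct unequal capture.

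**Working it through.** **1. The plan's own figures.** The article gives no event rate, capture rate or power for bleeding or stroke, so there is no plan figure to reproduce on this point. The sample size is used below only to set the scale. For 12.64% against 28%, two-sided alpha 0.05 and 90% power, the pooled formula gives 143 per arm. The design effect is 1 + (30 − 1) × 0.02 = 1.58, and 143 × 1.58 = 225.9, so 226 per arm or 452 in total, against 448 stated (within 1%). Then 448 / 0.90 = 497.8, so 498, as stated. An equal split is 448 / 2 = 224 per arm. That split is an assumption; the ratios below do not depend on it.

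**2. The two routes side by side.**

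| Month | Intervention arm | Control arm |
|---|---|---|
| No visit | Telephone contact | Telephone contact, same rule |
| Visit | No call; record of a visit with the CDSS branch available; questionnaire as needed | No call; record of a usual-care visit; questionnaire as needed |

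The routes differ only in the second row.

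**3. Formula.** If the true risk is the same in both arms, the recorded risk ratio is c_I / c_C, where c is the probability that an event is captured. Within an arm, c = w × c_visit + (1 − w) × c_phone, where w is the share of months with a visit. If w = 0 in both arms and calls work equally well, the ratio is 1.0. If w = 1, the ratio is that of the visit capture rates. With w the same in both arms and calls equally effective, the difference c_I − c_C is w times the difference at visits, so a gap confined to visits is diluted by the calls.

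**4. Illustration (all capture values and event rates assumed).** Here c_I = 0.90, there is no true difference, the true 12-month risk is 10%, and there are 224 patients per arm. Recorded events = 224 × 0.10 × c.

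| c_C | Recorded events, I v C | Recorded ratio | Chance of a significant excess in the intervention arm |
|---|---|---|---|
| 0.90 | 20.2 v 20.2 | 1.00 | 2.5% |
| 0.80 | 20.2 v 17.9 | 1.125 | 4.8% |
| 0.70 | 20.2 v 15.7 | 1.29 | 8.9% |
| 0.50 | 20.2 v 11.2 | 1.80 | 25.5% |

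The last column uses an effective size of 224 / (1 + 31 × 0.02) = 138.3 per arm, borrowing the ICC of 0.02 from the primary outcome. If the true risk is 5%, it becomes 2.5%, 4.0%, 6.2% and 14.5%. If it is 20%, it becomes 2.5%, 6.5%, 14.6% and 48.3%.

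**5. Effect on a real benefit.** With the same capture values, a true stroke/TIA risk ratio of 0.80 would be recorded as 0.80 × 0.90 / c_C, which is 0.80, 0.90, 1.03 or 1.44.

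The values in c_C are whole-year capture. By step 3, a low value needs both frequent visits and poor capture at those visits, so the bottom row is an extreme case.

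**The case against.** The strongest reply is that common sources exist. Questionnaire data are generated in each follow-up, signed and double-entered. The Auditing section has procedures checked at each follow-up in all 14 settings and incomplete questionnaires sent back. Medical-record data are to be requested from the district centres. None of this distinguishes the arms. If those questionnaires ask about bleeding and stroke, most of the problem goes. What they ask may be set out in a full protocol or case report form that is not shown, and its absence from an article is no fault. GPs in both groups are also trained in AF management, so control GPs may well ask.

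This stands in part: the size may be small, or zero. It does not dispose of the point, because the dependence of the call on visits and the as-needed condition on supplementary questionnaires are stated rules rather than omitted detail. The only scheduled patient questionnaire named measures satisfaction.

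Several stronger readings are tempting but not supported:

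- **That the safety comparison is biased.** The article shows an opening for unequal detection; it does not show that capture is unequal.
- **That the CDSS screens for events.** The text describes a referral branch. The interface figure is not shown, and no passage makes CDSS entries a source of outcome data.
- **That a common call by researchers is lost.** The caller is not named.
- **That hospital episodes of referred patients would be missing.** The coverage of the district data is not stated, so this is speculation.

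**Conclusion.** The point holds as a risk of differential detection of unknown size. Followed as written, the plan lets capture of minor bleeding and TIA differ by arm. Other stroke, major bleeding and AF-related admission are exposed to a lesser extent, and all-cause mortality very little. The primary outcome and the sample size are untouched.

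No magnitude can be taken from the document. Under assumed capture of 90% in the intervention arm and 90% down to 50% in the control arm, a null effect would be recorded as a ratio between 1.0 and 1.8. This rests on no true difference and on the intervention arm having the better capture. That direction is plausible given the CDSS branch, but it is not established. A reader should not infer that the whole safety comparison is invalid. The change is worth making because it is cheap and because the questions have to be asked while follow-up is running.

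**What to change.** In Enrollment and follow-up and in Data collection and management, remove the dependence on visits and the as-needed condition for event data. Ask every patient in both arms the same short set of questions on the same schedule, whether or not they visited: minor or major bleeding, stroke or TIA, and any hospital admission or emergency visit anywhere. The existing monthly contacts can carry these questions. At the least, attach them to the PSQ-18 at months 4, 8 and 12, accepting longer recall for minor events.

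Base the between-arm comparison of bleeding and stroke/TIA on this common source. Continue to report every event known from any source, including the CDSS, for safety, and add an all-source sensitivity analysis of the comparison. Nothing in the referral advice or other clinical management needs to change.

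The cost is a few minutes per contact. There is also a small chance that the questions prompt control GPs and so alter usual care. That is reduced if patients complete the form themselves, which should be practicable because patients unable to cooperate through illiteracy or dementia are already excluded.
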